### Outcomes

2.11.

Primary outcomes are: changes in HADS-anxiety and HADS-depression scores from pre-treatment to post-treatment and 6 months follow-up between treatment arms. Changes in the proportion of patients scoring below 8 on HADS-anxiety and HADS-depression, respectively, from pre-treatment to post-treatment and 6-months follow-up between treatment arms.

Secondary outcomes are changes in psychiatric disorders, rumination, worry, type D-personality, insomnia, quality of life and metacognitions scores, as well as CRP levels, from pre-treatment to post-treatment and 6-months follow-up between treatment arms. In addition, qualitative data will be collected and evaluated.

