### Sample size and power calculation

2.13.

Statistical power calculation was based on the primary outcome of HADS with subscale outcomes of HADS-depression and HADS-anxiety. A conservative anxiety/depression effect size from previous studies of individual and group ATT for depression was used (0.67). This effect size is similar to what has been reported in a meta-analytic study of CBT and other psychological treatments (0.67) (Cuijpers et al., 2010). Thus, based on previous research, we expected a difference between the two conditions (ATT and WLC) amounting to an effect size of approximately 0.67. Allowing for 15–20% drop out in accordance with previous studies, we aim for a final sample size of 32 in each group, i.e., 64 in total. This yields a statistical power above 90% using a two-sided significance test (*p* < 0.05).

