#### Quantitative analysis

2.14.1.

A repeated measures linear mixed-model will be used to estimate treatment effects for the combined sample, with HADS-A and HADS-D scores as outcomes, from pre-treatment, post-treatment and 6 months follow-up. Controlled effect sizes will be calculated in the following way: post treatment for immediate ATT minus post waiting list divided by the pooled standard deviation. Both ITT and per protocol analyses will be reported.

The primary reported analyses will be carried out as an intention-to-treat with all randomized participants. The analysis is supplemented with per-protocol analyses defined by participation in ≥4 of the 6 group-based sessions. Missing information on other co-variates will be permitted if there is <20% missing data for the co-variate in question. Age, gender, HADS-D and HADS-A scores will be entered in the models as covariates if baseline differences are observed.

An estimate of treatment effect size will be derived by comparing the wait-list control and intervention group on levels of symptoms of anxiety and depression (HADS), rumination (RRS), worry (PSWQ), insomnia (BIS), metacognitive beliefs (MCQ-30, PBRS, NBRS) and inflammation (CRP) at baseline, end of treatment and 6 months follow-up. False discovery rate will be applied for multiple testing (Benjamini and Hochberg, 1995).

Analyses will be undertaken using Stata SE vs. 18.0 (StataCorp, 2023) and/or R (R Core Team, 2021) and conducted by a statistician who will remain blind to group allocation throughout. A detailed statistical analyze plan (SAP) will be prepared and published prior to analyses taking place.

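### Four unranked primary variables at two timepoints are governed only by a false discovery rate rule, which gives no strong family-wise control of the primary claim, and the power statement assumes one test at 0.05

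*Protocol article*

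**What the plan says.** **Outcomes (2.11)** gives two sets of primary outcomes. The first is "Primary outcomes are: changes in HADS-anxiety and HADS-depression scores from pre-treatment to post-treatment and 6 months follow-up between treatment arms". The second is "Changes in the proportion of patients scoring below 8 on HADS-anxiety and HADS-depression, respectively, from pre-treatment to post-treatment and 6-months follow-up between treatment arms". That makes four variables at two timepoints, or eight comparisons. No lead variable, lead timepoint or order of testing is given.

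**Quantitative analysis (2.14.1)** describes comparing the arms, at end of treatment and at 6 months, on "levels of symptoms of anxiety and depression (HADS), rumination (RRS), worry (PSWQ), insomnia (BIS), metacognitive beliefs (MCQ-30, PBRS, NBRS) and inflammation (CRP"). The next sentence is the only multiplicity rule: "False discovery rate will be applied for multiple testing". Neither the family of hypotheses nor the level is stated. The same section promises a detailed SAP before analysis.

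**Sample size and power calculation (2.13)** says "Statistical power calculation was based on the primary outcome of HADS with subscale outcomes of HADS-depression and HADS-anxiety". It takes an effect size of 0.67 and 32 per arm, allows for 15–20% dropout, and states "This yields a statistical power above 90" per cent, "using a two-sided significance test (*p* < 0.05").

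**The concern.** The primary objective is to test whether ATT is effective, so the error rate that matters is the chance of a false claim on a primary outcome. The false discovery rate is a different quantity: the expected share of false findings among all findings. Under Benjamini-Hochberg the threshold for a HADS result moves with the number of other hypotheses rejected in the same family. If ATT shifts process measures such as rumination, worry or metacognition but not HADS, those successes loosen the HADS threshold. If the other measures are null, they tighten it and cost primary power.

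The power statement ignores this and uses one unadjusted test. An SAP that follows the article would inherit the unranked primaries, the error rate and the power figure.

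**Working it through.** **1. The plan's own power figure.** Inputs from 2.13: d = 0.67, n = 32 per arm, two-sided alpha 0.05.
- Noncentrality = d × √(n/2) = 0.67 × √16 = 2.68.
- Normal approximation: Φ(2.68 − 1.96) = Φ(0.72) = 76.4%. Noncentral t with 62 df: 75.1%.
- If 32 are randomised and 15–20% drop out, 32 × 0.85 = 27.2 and 32 × 0.80 = 25.6 remain. Noncentral t gives 67.6% for 27 and 65.9% for 26 per arm.
- For 90% power: n = 2 × (1.960 + 1.282)² / 0.67² ≈ 46.8, so 47 analysed per arm.

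The stated figure does not follow from the stated inputs. Baseline adjustment with a pre–post correlation of 0.6 would give 91.8% at 32 per arm (normal approximation), but the article states no such correlation.

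**2. Power at a split alpha.** At 0.025, the first Holm step for two tests: Φ(2.68 − 2.241) = 67.0%; noncentral t 65.0%.

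**3. How the Benjamini-Hochberg threshold moves.** The rule rejects up to the largest i with p(i) ≤ i × q/m. Assume q = 0.05.
- One timepoint: 4 primaries + 7 secondaries (RRS, PSWQ, BIS, MCQ-30, PBRS, NBRS, CRP), m = 11. With no other rejection, a primary needs p ≤ 0.05/11 = 0.0045. With all seven secondaries rejected, it needs p ≤ 8 × 0.05/11 = 0.036.
- Two timepoints: 8 + 14, m = 22. The same two thresholds are 0.05/22 = 0.0023 and 15 × 0.05/22 = 0.034.

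**4. Chance of at least one false primary finding.** Simulation with normal test statistics, q = 0.05, all primaries null, all listed secondaries affected at d = 0.67 (mean z = 2.68), common correlation ρ:

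| Family | ρ = 0 | ρ = 0.5 | ρ = 0.8 |
|---|---|---|---|
| 4 null primaries + 7 affected secondaries | 10% | 7% | 5% |
| 8 null primaries + 14 affected secondaries | 17% | 10–11% | 6% |

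If every null is true in the 22-test family, the figure is only 2.0–2.3%.

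Hand check of the ceiling, with secondaries so strong that they are always rejected and tests independent: 1 − (1 − 0.0364)⁴ = 13.8% and 1 − (1 − 0.0341)⁸ = 24.2%. Simulation gives 13.8% and 24.3%.

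**5. Without pooling.** Benjamini-Hochberg on the eight primaries alone, four null and four affected (for example, one subscale responds and the other does not):
- At d = 0.67: 8.8–8.9% (ρ = 0), 6.7–6.8% (ρ = 0.5), 4.7% (ρ = 0.8).
- With stronger effects and independent tests: about 11% at mean z = 3.5. The ceiling is 1 − (1 − 5 × 0.05/8)⁴ = 1 − 0.96875⁴ = 11.9%.

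**6. Power under the named rule.** With 22 tests and 32 per arm (ρ = 0.5 to 0), power per primary comparison is about 68–72% if all outcomes have d = 0.67, and 54–56% if only the primaries do.

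**The case against.** **The pooled family is inferred.** A reader might take the protocol to say that all four primary variables share one family with the secondaries. It does not say so. No family is named, the preceding sentence concerns effect-size estimates, and its list contains HADS scores but not the two proportions. Pooling is the natural reading, and the family could be settled in the SAP. This stands, but separating the primaries does not by itself restore strong control (step 5).

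**There is some 5% control.** A reader might infer that the primary claim has no 5% protection. Benjamini-Hochberg does keep the chance of any false finding at or below 5% when every null is true. What is missing is protection when some hypotheses are truly non-null.

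**The inflation can be small.** Taking all secondaries as affected while HADS is exactly null is unfavourable, since the article presents worry and rumination as drivers of distress. Each proportion is cut from the same HADS score, so independence is unrealistic. With only the two HADS scores as primaries and seven affected secondaries, the figure is about 4–7%. With three of seven secondaries affected and four null primaries, it is about 4–5%. Higher figures (11–18%) come from assuming z = 3.5, which at 32 per arm means d = 3.5/4 = 0.875, above the protocol's 0.67. The 8-and-14 row also needs secondary effects at 6 months, when both arms have had ATT. These points stand and are why a range is given.

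**Bonferroni figures are not the plan.** Power of 55% or 45% at 0.0125 or 0.00625 might be read as the planned analysis. It is not; step 6 gives power under the rule the article names.

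**Conclusion.** The point holds in this form: the article fixes several unranked primary variables and names an error rate that does not strongly control the chance of a false primary claim.

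The size is moderate and depends on assumptions. It is about 5–10% or 6–17% under pooling at d = 0.67, and about 5–9% (up to about 12% with stronger effects) if the eight primaries form their own family. The level q, the family and the correlations are assumptions, because the article states none of them.

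Separately, and without depending on those assumptions, the stated inputs give about 75% power at 32 analysed per arm (66–68% at 26–27), not above 90%. Correcting the alpha alone would not repair that statement. This does not show that the mixed model cannot reach 90%; it shows that the article gives no input from which that figure follows.

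**What to change.** - **Primary family.** Define it separately from the secondaries. Test HADS-A and HADS-D scores at the end of the randomised phase by Holm at two-sided 5%, and claim effectiveness for each subscale that passes.
- **Proportions and 6-month comparisons.** Test them afterwards in a fixed order, only if both scores have passed, or move them to secondary. The wait-list arm receives ATT after 6–8 weeks (Wait list control, 2.7), so the 6-month contrast is immediate versus delayed ATT.
- **Secondary outcomes.** Apply Benjamini-Hochberg to these only, with the family and level stated.
- **Power.** Restate it as about 75% at 0.05 and 65% at the first Holm step (0.025), for 32 analysed per arm without baseline adjustment. If a higher figure is claimed, give the correlation assumed.

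**Cost.** The testing order and families can go in the SAP promised before analysis. Moving outcomes to secondary is more than SAP wording: the trial was registered before inclusion and patients are already randomised, so it needs a documented protocol and registry amendment. The stated power becomes less favourable and the primary threshold somewhat stricter.

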#### Qualitative analysis

2.14.2.

Ten patients who have received ATT will be asked to participate in this qualitative study. The interviews will last for up to 60 min and will be conducted by KT. A phenomenological/hermeneutic approach will be used to analyze the data (Laverty, 2003). Thematic content analysis will be conducted to identify themes and patterns (Braun and Clarke, 2006). A semi- structured qualitative interview protocol has been developed for these purposes. This interview will cover the following themes: Experiences with ATT, experiences of processes that will be followed by improvement, experiences of aspects that might be unhelpful, and experiences with external factors (family, friends, work, school etc.) that will be important for improvement.

In-depths interviews will be analyzed by using Braun and Clarke’s 6 stage method for thematic analysis (Braun and Clarke, 2006). The transcripts will be read several times by the co-authors (KT and JM) to familiarize with the content and to form an overall impression of the material. The analysis will be deductive from the interview guide and supplemented inductively. Transcripts will be imported into the computer software NVivo 12 (QSR International Pty Ltd, 2018) a tool for analyzing qualitative data, for organizing and encoding data. Initial codes will be created based on statements of what was useful or what was not useful. The codes will be grouped into overarching themes, and sub-themes will be identified within those themes. The data analysis will be carried out by KT, in regular contact with JM and CP throughout the analysis process to discuss and redefine themes and sub-themes. Quotes from participants will been chosen to illustrate themes and sub-themes.

### Trial management

2.15.

Vestre Viken Trust is sponsor for this investigator-initiated trial which is part of the psychosocial project of the Norwegian Coronary Prevention (NORCOR) research group.^2^ The steering committee meets every 6 months to provide expert advice, supervise the overall projects, and monitor progress against milestones. A trial management group comprising the principal investigator (TD), the NORCOR principal investigator (JM), other supervisors (CP) and core personnel meet at least biweekly to monitor progress and be responsible for the day-to-day management of the project. There is also a user group with CHD patients, general practitioners, cardiac nurses, and user-representatives from patient organizations who have provided feedback on the study design and other aspects of the protocol. They will also contribute to disseminate the results and other trial related activities.

### Data management

2.16.

Data collection and coordination will be conducted by the study coordinator under the responsibility of the principal investigator.

### Trial status and timeline

2.17.

The first patient was randomized November 30th 2022 and per May 2023 10 out of 64 patients have been included and followed-up. A conservative estimate is that all 64 patients may be enrolled over a 2 year period. Thus, the final results of primary endpoint are expected in December 2024.

### Study safety

2.18.

We are not aware of any side-effects of ATT and no side-effects or serious events have been reported in previous ATT studies. However, group-ATT will be delivered by a health professional, who will monitor all study participants who attend the group sessions for any potential serious or adverse events. If any should occur during the treatment, the participants will be offered individual counseling and referral for relevant treatment elsewhere if considered indicated.

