### Wait list control

2.7.

This will involve monitoring patients waiting to receive ATT for a period of 6–8 weeks. These patients may access on demand follow up consultation at general practitioners. At the end of this period, patients will be re-assessed prior to being allocated to receive group ATT.

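### The only adverse-event ascertainment described is tied to attending group sessions, so adverse and serious events cannot be compared fairly between arms in the randomised period

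*Protocol article*

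**What the plan says.** Section 2.18 (Study safety) is the article's only provision on adverse events. The observer is the health professional delivering group ATT, "who will monitor all study participants who attend the group sessions for any potential serious or adverse events". The response is likewise tied to treatment: "If any should occur during the treatment, the participants will be offered individual counseling and referral for relevant treatment elsewhere if considered indicated".

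Section 2.7 (Wait list control) describes the comparator: "This will involve monitoring patients waiting to receive ATT for a period of 6–8 weeks". The contact it then specifies is access to primary care, "These patients may access on demand follow up consultation at general practitioners", and one re-assessment: "At the end of this period, patients will be re-assessed prior to being allocated to receive group ATT". It does not mention adverse events.

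Table 1 has no adverse-event row, and section 2.11 (Outcomes) lists no harms outcome. Section 2.14.1 bases the primary analysis on all randomised participants.

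**The concern.** Ascertainment through session attendance depends on allocation. During the randomised comparison one arm meets a health professional weekly, and the other has no sessions. Within the ATT arm, a patient who stops coming because of deterioration or a cardiac event leaves the stated route when there is something to record.

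The introduction describes raised cardiovascular risk in CHD patients with depression or anxiety, so background events are plausible in both arms. If events are recorded mainly where sessions take place, a by-arm count mixes the effect of ATT with the effect of being asked. Without a count from untreated patients, events seen at sessions cannot be set against a background rate. A finding of no events would describe attenders only.

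**Working it through.** The plan states no figure on this point, so there is none to reproduce. The check has two parts.

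**1. Who is covered, and when**

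| Group and period | Stated ascertainment of adverse or serious events | Source |
|---|---|---|
| ATT arm, while attending the six weekly sessions | Yes, by the health professional delivering ATT | 2.18, 2.6 |
| ATT arm, after stopping attendance | None stated | 2.18 |
| Wait-list arm, 6–8 week wait | None stated; on-demand general practitioner access and one re-assessment | 2.7 |
| Wait-list arm, while attending ATT later | Yes, but no longer untreated | 2.7, 2.18 |
| All patients, last session to 6 months | None stated | 2.18, Table 1 |

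Two other places might close the gap:

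- Section 2.7 uses the word monitoring for waiting patients. It gives no adverse-event purpose, person, method or route from general practitioner to trial.
- Section 2.10 lets the principal investigator withdraw a participant who needs urgent treatment, for example hospitalisation. That is a withdrawal rule. It does not say that such events are sought or recorded.

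The Table 1 timing marks are not legible in the text available, but the check needs only the row labels.

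**2. Size of the distortion (illustration)**

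Input from section 2.13: "we aim for a final sample size of 32 in each group, i.e., 64 in total". In the randomised period, 32/64 = 50% of patients have no sessions.

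Assumptions, not from the documents: the same true proportion of affected patients *p* in both arms; detection probability *s* of 0.5 to 1 through sessions and 0 in the wait-list arm.

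Truly affected per arm = 32 × *p*. Expected recorded in the ATT arm = 32 × *p* × *s*.

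| *p* | Truly affected, each arm | Recorded, ATT (*s* = 0.5 to 1) | Recorded, wait-list |
|---|---|---|---|
| 5% | 1.6 | 0.8 to 1.6 | 0 |
| 10% | 3.2 | 1.6 to 3.2 | 0 |
| 20% | 6.4 | 3.2 to 6.4 | 0 |

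The true difference is zero in every row, so the recorded difference comes wholly from ascertainment. Zero detection in the wait-list arm is the literal reading of section 2.18. If some events surface at the re-assessment, the distortion is smaller.

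**The case against.** The strongest reply is that section 2.18 says what the group health professional does and does not say that nobody else records events. A condensed article commonly leaves serious-event forms and reporting routes to the full protocol, and the word monitoring in section 2.7 may refer to such a procedure. This stands in part: the article does not prove that waiting patients go unobserved. But it is not simply silent. It names a monitored population, and that population is narrower than the one analysed. If the full protocol collects events from everyone, section 2.18 misdescribes it and needs correcting.

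Several stronger readings are tempting, and the documents do not support them:

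- **That psychiatric worsening is captured in one arm only.** HADS-A and HADS-D are primary outcomes and psychiatric disorders a secondary outcome, all compared between arms under section 2.11.
- **That the trial will report ATT as harmful or as free of side-effects.** No by-arm harms report is announced, and the remark on absent side-effects in section 2.18 concerns earlier studies.
- **That the planned dropout gives the number of ATT patients lost to event monitoring.** The wording is "Allowing for 15–20% drop out in accordance with previous studies". It concerns study dropout, not missed sessions, and patients are observed while they still attend. No upper bound on the event rate should be built on it.
- **That wait-list patients are never monitored.** They come under section 2.18 once they attend ATT.

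It is also fair to say that with 32 per arm and few events, even a perfectly ascertained comparison would be imprecise. Imprecision can be shown with an interval. Unequal ascertainment cannot be removed in the analysis.

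**Conclusion.** The concern holds for adverse and serious events as such. The stated ascertainment follows session attendance, so it differs by arm in the only period with an untreated comparator and stops for ATT patients who cease to attend. It also leaves everyone uncovered after the last session. A fair by-arm comparison of these events is not possible from the plan as described.

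The wait-list gap concerns 32 of 64 patients for 6–8 weeks. Under the assumed rates of 5% to 20%, between 0.8 and 6.4 affected ATT patients would be recorded against none waiting, with no true difference.

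The conclusion rests on reading section 2.18 as the complete description of event collection. It does not affect the primary HADS estimate. This is an inexpensive improvement that should be made, not a flaw that undermines the trial.

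**What to change.** 1. Ask every randomised patient the same structured adverse-event and serious-adverse-event question at the existing post-treatment or end-of-wait assessment and at 6 months, regardless of session attendance. Have it cover the time since randomisation or since the last assessment, with event dates, because the wait varies from 6 to 8 weeks.
2. Tabulate the answers by arm for the randomised period, using all randomised patients and showing how many answered. Present the 6-month answers descriptively, since both arms have been offered ATT by then.
3. Report events noticed during sessions separately, so that they do not enter the between-arm count.
4. Reconcile sections 2.7 and 2.18: state whether monitoring of waiting patients includes adverse events and, if so, who records them and how.

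The cost is one added form and one table, with no extra visits. Coverage will be incomplete. Patients who have withdrawn may not be reachable, and section 2.17 reports 10 of 64 already included and followed up by May 2023. At that date 64 − 10 = 54 could still have been asked prospectively; the number falls as enrolment proceeds.
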